### Sample size and sampling

2.6

The central limit theorem posits that a minimal sample size of 30–40 is enough for determining the mean, standard deviations, and 95% confidence intervals (58). This pilot RCT aims to assess the feasibility, acceptability, and preliminary effectiveness of the AOMI intervention, utilizing a generally acceptable sample size for preliminary analysis to evaluate intervention feasibility and estimate the between-group effect. Specifically, each study group will have 18 individuals to identify a standardized effect size of 0.40 with 80% power and a two-sided significance level of 5% (59). Taking into account a potential attrition rate of 20%, 23 participants per group (i.e., 46 participants in total) will be recruited by using convenience sampling. For one-on-one interviews, we will use a purposeful sampling of key informants, including those who completed at least 60% of the intervention sessions and those who did not, until we reach information saturation and find no relevant new codes in the data (60).

For MRI scans, a liberal threshold of *α* = 0.05 requires 24 participants (12 per group) to achieve 80% power at the single-voxel level for typical activations (61). To control error rates in multiple comparisons, doubling the number of participants is recommended to maintain this level of power. Due to the challenges of MRI data collection, each group will consist of a minimum of 12 participants undergoing pre- and post-intervention MRI scans. Notably, this sample size aligns with the median sample size observed in highly cited clinical fMRI studies published over the last three decades (62).

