#### Quantitative data analyses

2.7.1

Quantitative data analyses will be conducted using IBM SPSS Statistics for Windows (Version 26.0. Armonk, NY: IBM Corp), with all statistical tests being two-sided and significance set at 0.05. The outcomes will be analyzed with an intention-to-treat approach (63). As for statistical description, the count data, such as gender will be presented as “frequency” and “percentage.” The continuous data that conform to the normal distribution (assessed by the W test coupled with a histogram) will be described using means ± standard deviation. As for group differences at baseline, post-intervention, and follow-up, *t-test* or Mann–Whitney *U* test will be performed for continuous variables; Pearson χ2 tests or Fisher exact test will be used for dichotomous variables. The generalized estimating equation (GEE) model, which could test the effects of group, time, and their interactions, will be used to analyze the effects of the intervention. Covariance (if any found in the baseline comparison) will be adjusted during the analysis of intervention effects. Cohen’s *d* will be used as the unit measure of effect size, and is interpreted as follows: 0.2 represents a small effect, 0.5 a moderate effect, and 0.8 a large effect. Cohen’s *d,* calculated by using the formula “difference in treatment and control group means divided by the pooled standard deviation,” is applicable for small sample sizes (64).

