This pilot RCT adopts a multidisciplinary approach, incorporating psychological, neurological, and neuropsychological assessments. The utilization of multimodal MRI enables a better understanding of the neural mechanism behind the AOMI and post-SCI neuroplastic changes. These findings will establish an empirical foundation for developing mechanism-driven interventions targeting cognitive impairment and depression in adults with SCI.

This study has several limitations that should be acknowledged. First, this pilot RCT can only show the preliminary effectiveness of the home-based AOMI intervention. Furthermore, the small sample size and potential selection bias resulting from convenience sampling may limit the generalizability of the findings. However, the results of this pilot study will provide valuable insights for designing a future full-scale RCT, which could generate much-needed level one evidence regarding the effectiveness of AOMI. Second, due to the inherent nature of the intervention, neither the interventionists nor the participants could be effectively blinded. Although we will implement weekly phone monitoring of intervention adherence and design an active control condition, potential performance bias may remain a limitation. Third, a defining characteristic of AOMI is the absence of overt physical actions during the imagery process. This inherent feature makes objective performance evaluation challenging, as AOMI relies on mental movement representation. We will employ qualitative methods (i.e., training diaries and post-intervention interviews) to assess whether participants really engaged in AOMI and whether they truly imagined the intended content. However, integrating objective methods such as neuroimaging techniques would better evaluate intervention fidelity. Due to resource constraints, we will consider this monitoring method in future research.

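### The small-sample justification for uncorrected Cohen's d points the wrong way: the formula is biased upward on average, by about 2% at this trial's size, and a fixed multiplier removes the bias

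*Protocol article*

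**What the plan says.** Section 2.7.1 (Quantitative data analyses) makes Cohen's d the effect-size measure and gives its formula in words: "difference in treatment and control group means divided by the pooled standard deviation". It adds that d so calculated "is applicable for small sample sizes", with one citation. It reads the result against fixed bands, where "0.2 represents a small effect, 0.5 a moderate effect, and 0.8 a large effect". It mentions no correction factor.

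Section 2.6 (Sample size and sampling) gives the sizes at which d will be computed: 18 evaluable per group, then "Taking into account a potential attrition rate of 20%, 23 participants per group (i.e., 46 participants in total) will be recruited". The same section says that the sample is meant to "evaluate intervention feasibility and estimate the between-group effect", so an effect estimate is one of the pilot's intended products.

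**The concern.** The formula and the reason for it are both written down, so this is not a detail left to an analysis plan that is not shown. Suitability for small samples is the only property claimed for the formula. Yet the mean difference divided by the pooled standard deviation is close to unbiased only when samples are large. The pooled standard deviation enters through its reciprocal, and the expected reciprocal exceeds the reciprocal of the true value. The expected d therefore lies further from zero than the population effect, and the gap widens as the sample shrinks. The usual small-sample version is the same quantity times a factor below 1 (Hedges' g).

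At stake is a small systematic error in the measure that serves the stated aim of estimating the between-group effect. It acts away from zero for every outcome reported this way, including depression, where benefit is a negative difference on the BDI-II.

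**Working it through.** **Inputs.** The formula is that of section 2.7.1. The group sizes are 18 and 23 per arm, from section 2.6. The planning effect of 0.40 is also from section 2.6 and is used here only as an example of a true effect. Normal data, equal variances and equal arms are assumed.

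**The plan's own figures.** The attrition step reproduces: 18/(1 − 0.20) = 22.5, rounded up to 23. The 18 per group does not follow from 0.40 read as a standardized difference between two means, which needs 99 per arm for 80% power at two-sided 5%. That is a separate and much larger issue. The bias calculation below takes 18 and 23 as given and does not depend on it.

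**Correction factor.** With df = 2n − 2,

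J = Γ(df/2) / [√(df/2) × Γ((df − 1)/2)], approximately 1 − 3/(4df − 1).

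The expected d is δ/J, so the average inflation is 1/J − 1. The corrected estimate is g = J × d, which averages δ.

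- 18 per arm: df = 34; approximation 1 − 3/135 = 0.9778; exact J = 0.9778; inflation 1/0.9778 − 1 = 2.3%.
- 23 per arm: df = 44; approximation 1 − 3/175 = 0.9829; exact J = 0.9828; inflation 1/0.9828 − 1 = 1.7%.

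**On the d scale.** For a true 0.40, the expected d is 0.40/0.9778 = 0.409 at 18 per arm and 0.40/0.9828 = 0.407 at 23 per arm. The average bias is +0.009 and +0.007.

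**Against sampling error.** SE(d) is approximately √(2/n + d²/(4n)).

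- 18 per arm: √(2/18 + 0.16/72) = 0.337; bias/SE = 0.0091/0.337 = 2.7%.
- 23 per arm: √(2/23 + 0.16/92) = 0.298; bias/SE = 0.0070/0.298 = 2.3%.

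**Simulation** (200,000 replicates of normal data, true effect 0.40).

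| Per arm | Mean d | Median d | d above 0.40 | Central 95% of d | Mean g |
|---|---|---|---|---|---|
| 18 | 0.410 | 0.403 | 50.3% | −0.25 to 1.11 | 0.401 |
| 23 | 0.408 | 0.403 | 50.4% | −0.18 to 1.02 | 0.401 |

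The means agree with theory within simulation error.

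**Effect on the bands.** At 18 per arm the correction changes the label only if d lies between a cut-off and that cut-off divided by 0.9778: 0.200 to 0.205, 0.500 to 0.511, or 0.800 to 0.818. These intervals are narrow beside a standard error of about 0.34.

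**The case against.** The best defence is that applicable does not mean unbiased. The article does not claim that d is free of bias and does not compare it with a corrected version. Pooled-SD d is a standard, fully specified measure that anyone with the group sizes can convert to g. The cited source is not at hand, so what it says about small samples cannot be checked. This defence limits the weight of the point, but it does not rescue the reason given: small sample size is the condition under which the uncorrected formula performs worst. The absence of a confidence interval for d is not a fault of the article either, since that detail may sit in an analysis plan not shown.

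Three stronger readings are tempting, and the documents do not support them.

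- A reader might infer that the reported effects will be overstated. The bias is a property of the average. A single d exceeds the truth in only about half of trials.
- A reader might infer that an inflated d will be carried into the full-scale trial and make it too small. The Discussion says only that the results will "provide valuable insights for designing a future full-scale RCT". Nothing says that the observed d will set a later sample size. Even if someone took that step with the average d for a true 0.40, the result would be 94 or 95 per arm instead of 99, and power of 78.3% or 78.7% instead of 80%.
- A reader might extend the point to the smaller MRI subset, where the bias would be larger. Section 2.7.3 (MRI data analysis) plans no Cohen's d for those data.

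**Conclusion.** The point holds as a minor one. The article fixes an uncorrected estimator and supports it with a reason that argues for the correction. The average bias is about 2% of the effect (2.3% at 18 per arm, 1.7% at 23), or about 0.01 on the d scale for a true 0.40. Imprecision limits what this pilot's d can tell a reader far more than bias does. The generalized estimating equation analysis and the group comparisons do not use d, so no test result changes.

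The figures assume normal data, equal variances, equal arms, and d computed from raw group means and the pooled standard deviation with df = n1 + n2 − 2. Skewed scores would change the exact values.

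**What to change.** In section 2.7.1, replace uncorrected Cohen's d with Hedges' g = d × (1 − 3/(4df − 1)), where df = n1 + n2 − 2 for the participants actually contributing to that comparison, and report it with its 95% confidence interval. Delete the statement that the uncorrected formula suits small samples. The interpretation bands can stay.

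The cost is one line of text. Reported effects become about 2% smaller in magnitude. Recruitment, data collection, sample size and hypothesis tests are unchanged. The interval is the more useful half of the change, because it shows how little a pilot of this size can pin down the effect.

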#### Missing data management

2.7.2

The Little’s Missing Completely at Random test will be used to assess whether the missing values in a specific variable are unrelated to any other observed or unobserved variables (65). If the mechanism is missing at random, the multiple imputation will be conducted for handling the missing data due to its advantages of valid statistical inference even in the presence of a small sample size (66). For the GEE analysis, missing values are not imputed, as GEE can accommodate missing data and provides a natural way to deal with missing values (67).

#### MRI data analysis

2.7.3

To acquire preliminary data on the association between the interventions and MRI metrics, per-protocol analyses will be conducted. Per-protocol analyses will include only those participants who complete at least 60% of the intervention sessions. Brain tissue total volume, gray matter, and white matter volumes, normalized for subject head size, will be estimated with SIENAX (part of FMRIB’s Software Library (FSL) 5.0.9). The tissue-type segmentation with partial volume estimation will be carried out to calculate the total volume of brain tissue (including separate estimates of volumes of gray matter and white matter). We will use Statistical Parametric Mapping 12 (SPM12) and the functional connectivity toolbox (CONN 20.b) in MATLAB 2021b for standard fMRI preprocessing and denoising procedures. Additionally, denoising will be achieved through linear regression to account for confounding effects. Finally, we will apply band-pass filtering [0.008, 0.1 Hz] to the blood-oxygen-level-dependent signals to focus on slow-frequency fluctuations while minimizing the influence of non-physiological, head-motion, and other noise sources (68).

To analyze fMRI data, differences of each group at baseline and post-intervention will be evaluated using the paired *t-test* in Statistical nonParametric Mapping (SnPM); differences between groups (intervention group vs. control group) will be assessed using a two-sample *t-test*. Differences between the two groups of the study over time will be evaluated using a General linear model, in which group and time will be included as distinct factors (2 × 2 factorial design). Multiple linear regression models will be used, with age, education level, and motor imagery ability as covariates, to assess the correlation between changes in MRI results and changes in cognitive function and depression data after intervention (69). For DTI data, statistical analyses will be performed using non-parametric permutation testing with 5,000 Monte Carlo simulations. We will look for differences in fractional anisotropy between the groups, accounting for age, educational level, and motor imagery ability as regressors of no interest in the general linear model. A two-sample *t* test will be used to evaluate the between-group differences in DTI metrices (e.g., path length, clustering coefficient, global efficiency, local efficiency, strength, and small world attribute). Association analysis between altered white matter microstructure imaging data and the assessments of cognitive function and depression will be analyzed with Spearman’s correlation coefficient (70).

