### Outcome measures

2.5

A trained research assistant, blinded to group allocation, will conduct a series of assessments at three time points: baseline (T0), after the 8-week intervention program (T1), and 1 month post-intervention (T2). Socio-demographic variables, feasibility and acceptability indexes, and effect outcomes are included. The effect outcomes include primary outcomes (global cognitive function and depression) and secondary outcomes (neurocognitive domains, multimodal MRI findings, chronic pain, self-efficacy for exercise, and motor imagery ability). The assessments will be conducted during participants’ visits to the study site (University campus) (Table 1).

**Table 1 tab1:** Data collection schedule.

Assessment items	Study period			
	Enrollment	Allocation	Post-allocation	
	−T1	T0 Baseline	T1 Post-intervention	T2 1-month follow-up
Enrollment				
Eligibility screening	X			
Informed consent	X			
Allocation		X		
Assessments				
Socio-demographics and medical history		X		
Feasibility of the intervention		X		X
Acceptability of the intervention			X	
Intervention effectiveness				
Primary outcomes				
Global cognitive function		X	X	X
Depression		X	X	X
Secondary outcomes				
Cognitive domain-attention		X	X	X
Cognitive domain-executive function		X	X	X
Multimodal MRI findings		X	X	
Chronic pain		X	X	X
Self-efficacy for exercise		X	X	X
Motor imagery ability		X	X	X

MRI, magnetic resonance imaging.

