#### Feasibility and acceptability

2.5.2

The feasibility indices include the recruitment rate, which is the percentage of participants who give consent after determining their eligibility; the retention rate, which refers to the number of participants who complete the study divided by all participants who agree to consent; and the dropout rate, which is the number of participants who drop out after randomization divided by all participants who agree to consent (39). The acceptability of the intervention will be indicated by (1) adverse event records related to the AOMI intervention; (2) intervention satisfaction, evaluated through the 8-item Client Satisfaction Questionnaire with a four-point Likert scale (40) and a qualitative interview. The one-on-one interviews will be conducted by a research assistant trained in qualitative research and possessing a background in psychology; (3) adherence rate, measured as the percentage of participants completing a minimum of 60% of interventions, equivalent to at least 15 sessions.

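### The only analysis set named for the MRI secondary outcome is a per-protocol set defined by adherence after randomisation, which is not reconciled with the general intention-to-treat statement and has no allowance in the MRI sample size

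*Protocol article*

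**What the plan says.** All references are to the protocol article.

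- **Status of MRI.** Section 2.5 (Outcome measures) places MRI among the effect outcomes: "secondary outcomes (neurocognitive domains, multimodal MRI findings, chronic pain, self-efficacy for exercise, and motor imagery ability". Table 1 schedules it at baseline and post-intervention.
- **General analysis population.** Section 2.7.1 (Quantitative data analyses): "The outcomes will be analyzed with an intention-to-treat approach". No outcome is exempted.
- **MRI analysis population.** Section 2.7.3 (MRI data analysis): "To acquire preliminary data on the association between the interventions and MRI metrics, per-protocol analyses will be conducted". The next sentence defines the set: "Per-protocol analyses will include only those participants who complete at least 60% of the intervention sessions". No other MRI set is named in that section.
- **The threshold in sessions.** Section 2.5.2 (Feasibility and acceptability) describes the same level as "completing a minimum of 60% of interventions, equivalent to at least 15 sessions".
- **Use of the MRI data.** Section 2.7.3 goes on to two-sample tests between the arms, a 2 × 2 group-by-time model, and group differences in fractional anisotropy and other DTI measures.
- **MRI sample size.** Section 2.6 (Sample size and sampling) says that an alpha of 0.05 "requires 24 participants (12 per group) to achieve 80% power at the single-voxel level for typical activations". It adds: "To control error rates in multiple comparisons, doubling the number of participants is recommended to maintain this level of power". It then settles, citing the difficulty of collecting MRI data, on the following: "each group will consist of a minimum of 12 participants undergoing pre- and post-intervention MRI scans".

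**The concern.** The between-arm MRI comparison is the one that would link a change in the brain to AOMI, and it draws its force from randomisation. Completing 60% of sessions is known only after randomisation, and the sessions differ between arms. One arm practises effortful motor imagery at home; the other watches landscape videos. The people who persist with each need not be alike. The protocol itself gives reasons to expect a link with the outcomes: it limits AOMI sessions to 20 minutes to reduce mental fatigue (2.4.1), varies the imagery content to hold attention and support compliance (2.4.1), and notes that severe cognitive impairment can impair imagery ability (2.2).

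Three things are at stake. A group difference in MRI change could partly reflect who kept going. The clinical effects (intention-to-treat) and the MRI effects (adherers) would describe differently defined populations, although 2.7.3 relates changes in one to changes in the other. And a small MRI sample could become smaller, by losing scans already acquired.

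**Working it through.** **1. The text.** Section 2.7.1 gives a general rule without exception. Section 2.7.3 gives a different rule for one declared outcome and does not say that it departs from the general one. That 2.7.3 is the only MRI set is inferred from the absence of any other; the flow chart, whose caption expands ITT, is not shown.

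**2. The threshold.** 3 sessions × 8 weeks = 24 sessions; 0.60 × 24 = 14.4, rounded up to 15. This agrees with section 2.5.2.

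**3. The MRI sample size.** The figure of 12 per group for 80% power rests on a cited source, and the article gives no effect size or SD, so it cannot be reproduced. It can be back-solved. For a two-sample t-test at two-sided 5%, uncorrected, 80% power at 12 per group corresponds to d = 1.20 (noncentral t; 1.14 by normal approximation). The 12 are counted as participants scanned twice. The 20% attrition allowance in section 2.6 is applied to the main sample (18 to 23 per group), and no allowance for the 60% rule appears in the MRI figure.

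**4. Selection bias.** The share below 60% of sessions is not given, nor is any relation between adherence and MRI change. Both are assumed here. Suppose there is no true effect, that adherence propensity and MRI change are bivariate normal with correlation r, and that the fraction q with the lowest propensity is excluded. The mean of those who remain then shifts by

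r × φ(z_q) / (1 − q), in SD units.

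- q = 20%: 0.280 / 0.80 = 0.350
- q = 10%: 0.1755 / 0.90 = 0.195

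The spurious between-arm difference is r times the difference in these factors:

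| Excluded, arm A / arm B | r = 0.3 | r = 0.5 |
|---|---|---|
| 20% / 20%, same r in both arms | 0 | 0 |
| 20% / 10% | 0.3 × 0.155 = 0.05 SD | 0.5 × 0.155 = 0.08 SD |
| 20% / none | 0.3 × 0.350 = 0.105 SD | 0.5 × 0.350 = 0.175 SD |

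**5. Precision.** Detectable difference at 80% power (same test) and power at d = 1.20, for 12 scanned per group:

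| Analysed | Detectable d | Power at d = 1.20 |
|---|---|---|
| 12 and 12 | 1.20 | 80% |
| 12 and 10 | 1.26 | 76% |
| 10 and 10 | 1.32 | 72% |

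The row with 12 and 10 goes with exclusions in one arm only, and the row with 10 and 10 with equal exclusions in both. The largest bias and the largest loss of precision therefore belong to different scenarios and should not be added together. These figures are for a single voxel without correction for multiple comparisons.

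**6. Scans needed to keep 12 per group under the 60% rule.** 12 / (1 − q), rounded up: 14 at 10% exclusion, 15 at 20%, 18 at 30%, 20 at 40%.

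**The case against.** The strongest reply is that section 2.7.3 is a deliberate exception. The intention-to-treat sentence stands in a section about SPSS, t-tests and GEE, while MRI has its own section, software and tests, and a specific rule normally overrides a general one. The stated purpose is preliminary data, the trial is a pilot, and asking what changes in people who actually trained is a fair mechanistic question. This largely stands, and it is why a reader who infers an outright contradiction goes further than the text supports. What remains is that the exception is never declared, and that a per-protocol set can supplement a between-arm comparison but is a weak sole basis for one.

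A reader might also infer that the rule breaks randomisation and that analysing all scanned participants would restore it. Neither follows. Section 2.6 plans for a minimum of 12 scanned out of 23 per group and does not describe how they are chosen, and attending the second scan is itself an event after randomisation. The 60% rule adds a layer of selection to a set that may already be selected; removing it takes away that layer only.

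Finally, a reader might take the loss of scanned participants as certain. It is not. Twelve is a minimum and more may be scanned, weekly calls support adherence, 15 of 24 sessions is not a demanding threshold, and people who stop early may never have a second scan. The additional exclusions could be few or none. Even the largest bias shown is small beside a detectable difference of 1.2 SD.

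**Conclusion.** The point holds in a limited form. A declared secondary outcome is compared between randomised arms on a set defined by adherence, no other MRI set is named, and the intention-to-treat statement is not qualified to allow for it. The textual part is secure. The size of the harm is not: it rests on assumed exclusion rates and an assumed correlation of 0.3 to 0.5, and within those assumptions it runs from no bias to 0.175 SD, with a detectable d between 1.20 and 1.32. The primary outcomes, global cognitive function and depression, are not affected. This should be corrected, but it does not threaten the trial's main aims.

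**What to change.** Reconcile sections 2.7.1 and 2.7.3:

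1. Define the main MRI between-arm comparison as all participants with usable pre- and post-intervention scans, in the arm assigned, whatever number of sessions they completed. Say openly that this is still a subset of those randomised, and describe how participants enter the MRI subset.
2. Keep the set with at least 60% of sessions as a labelled supplementary analysis, and report by arm how many scanned participants it excludes.
3. Describe the MRI results as exploratory.
4. In section 2.6, state whether the minimum of 12 per group refers to participants scanned or participants analysed.

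The cost is a few sentences and one further run of the same pipeline on scans already acquired. No additional scanning is needed, because the main set no longer depends on adherence.

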Multimodal MRI will be used to uncover possible mechanisms underlying the effectiveness of the AOMI intervention. The brain scanning session lasts around 40 min and includes the following sequences: T1-weighted anatomical scan for regional volume measurement, resting-state functional MRI (rs-fMRI) for assessing functional connectivity features and neural networks, task-based fMRI to indicate specific brain regions activated during AOMI tasks, and diffusion tensor imaging (DTI) to reflect the microstructural integrity of white matter tracts (53). During the rs-fMRI scan, subjects will be instructed to lie at rest with eyes open and fix on a bright cross-hair on a dark background. During the task-based fMRI, the subjects will be instructed to perform an “AOMI” fMRI task: subjects will be asked to imagine themselves performing the same exercise while watching the video representing wheelchair exercises. Videos will be presented from a dual perspective (first-person and third-person), and subjects will be asked to identify themselves and mentally simulate each situation (without moving the body). AOMI videos are alternated with resting periods in which subjects will be instructed to observe a static picture from the videos. The main acquisition parameters for each modality are listed in Supplementary Table S4. The multimodal MRI scans will be completed at the University Research Facility in Behavioral and Systems Neuroscience pre- and post-intervention on a 3-Tesla Siemens Prisma scanner, with a 32-channel head coil.

*Chronic pain*: The Chinese version of the Brief Pain Inventory (BPI-C) will be used to assess pain severity and interference (54). This questionnaire has been used in patients with SCI, with higher scores representing more violent pain (55).

*Self-efficacy for exercise*: The 9-item Chinese version of the self-efficacy for exercise (Cronbach’s *α* = 0.90) will be used to evaluate participants’ confidence level (from 0, not confident, to 10 very confident) regarding engaging in regular exercise (56). A higher score indicates greater exercise self-efficacy.

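### The MRI-change regressions name their covariates without group and do not say whether the arms are pooled, and the white-matter correlation names no group adjustment

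*Protocol article*

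**What the plan says.** The purpose of the imaging is given under Secondary outcomes (2.5.3.2): "Multimodal MRI will be used to uncover possible mechanisms underlying the effectiveness of the AOMI intervention".

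Section 2.7.3 (MRI data analysis) then sets out several separate analyses:

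- For fMRI there are within-group paired tests, between-group two-sample tests, and a general linear model "in which group and time will be included as distinct factors (2 × 2 factorial design").
- Change is related to change by multiple linear regression "with age, education level, and motor imagery ability as covariates, to assess the correlation between changes in MRI results and changes in cognitive function" and in depression. Three covariates are named, and group is not one of them.
- For white matter: "Association analysis between altered white matter microstructure imaging data and the assessments of cognitive function and depression will be analyzed with Spearman’s correlation coefficient". No adjustment or stratification by group is named.

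The analysis set for the imaging work is per-protocol: "Per-protocol analyses will include only those participants who complete at least 60% of the intervention sessions". The Sample size and sampling section (2.6) says that "each group will consist of a minimum of 12 participants undergoing pre- and post-intervention MRI scans". The significance rule in 2.7.1 is stated "with all statistical tests being two-sided and significance set at 0.05".

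The article does not say whether the change-on-change regressions and the Spearman correlations combine the arms, are run within each arm, or use the intervention arm only.

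**The concern.** If AOMI moves both an MRI measure and cognition or mood, the treated participants sit higher on both axes (or in opposite directions, depending on the scoring) and the controls sit lower. Pooled, the two clouds of points line up and give a correlation, even if, within each arm, people with more MRI change do no better than people with less. A regression without group cannot tell a brain–behaviour link from two parallel effects of treatment.

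The named covariates do not help. Age, education level and motor imagery ability are the three minimization factors in section 2.3, so the allocation is designed to balance them between arms. Adjusting for them removes essentially none of an arm difference in the changes.

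What is at stake is how the mechanism result is read. The artefact grows with the intervention's success on both measures, which is when a mechanistic interpretation is most tempting.

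**Working it through.** **Inputs from the article.** At least 12 scanned per arm (2.6); 23 randomised per arm (2.6); two-sided 5% (2.7.1); three covariates, no group (2.7.3); planned standardized effect 0.40 (2.6, main sample size). No effect size is given for MRI change, so every arm difference below other than 0.40 is an assumption, and applying 0.40 to MRI change is one too. The only sample size figure tied to the imaging analyses, 24 scanned, cannot be reproduced because no voxel-level effect or variance is given. Nothing here depends on it or disputes it.

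**Step 1: induced correlation, closed form.** Let d1 and d2 be the arm differences in MRI change and outcome change, in within-arm SDs, with 1:1 allocation and zero correlation within arms. The group indicator has variance 1/4, so the pooled covariance is d1·d2/4 and the pooled variances are 1 + d1²/4 and 1 + d2²/4. Hence

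r = (d1·d2/4) / √[(1 + d1²/4)(1 + d2²/4)].

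- d1 = d2 = 0.4: 0.04/1.04 = 0.04
- d1 = d2 = 0.8: 0.16/1.16 = 0.14
- d1 = d2 = 1.2: 0.36/1.36 = 0.26
- d1 = 0.8, d2 = 0.4: 0.08/√(1.16 × 1.04) = 0.07
- either d equal to 0: r = 0

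**Step 2: rejection rate of the 5% test.** Simulation with 20,000 data sets per setting: normal changes with no within-arm association, least squares of outcome change on MRI change plus three covariates unrelated to either, with and without a group term. The Monte Carlo standard error near 5% is √(0.05 × 0.95/20,000) = 0.15 percentage points.

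| Arm difference, MRI / outcome (SD) | Induced r | No group, 12 per arm | No group, 23 per arm | With group, 12 per arm |
|---|---|---|---|---|
| 0 / 0 | 0.00 | 4.9% | 5.1% | 4.9% |
| 0.4 / 0.4 | 0.04 | 5.3% | 5.7% | 5.1% |
| 0.8 / 0.4 | 0.07 | 6.1% | 7.5% | 4.8% |
| 0.8 / 0.8 | 0.14 | 9.2% | 13.9% | 5.1% |
| 1.2 / 1.2 | 0.26 | 22.3% | 42.2% | 5.1% |

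The 23-per-arm column is a ceiling. It needs every randomised participant to be scanned twice and to meet the session threshold, while section 2.6 itself allows for 20% attrition and commits to only 12 per arm for MRI.

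**Step 3: cost of the group term.** At n = 24 the model without group has five coefficients (intercept, MRI change, three covariates), leaving 24 − 5 = 19 residual degrees of freedom; with group it has 18. Separate within-arm models at 12 per arm would leave 12 − 5 = 7 each. These counts treat education as a single term.

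The simulation covers the regressions only. The same mechanism applies to a pooled Spearman correlation, but its size was not simulated.

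**The case against.** The strongest reply is that pooling is not stated. The same paragraph opens with within-group comparisons, so regressions run arm by arm are possible, and then the artefact does not arise. A reader might infer from the covariate list that the plan pools the arms; the text does not say so. Pooling remains the natural reading, because the sentence follows directly on a two-group model, no within-arm or single-arm analysis is named, and four predictors on 12 people would leave 7 degrees of freedom. But it is an inference.

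A second reply is that a condensed article may leave model terms to a fuller document. That carries less weight here: the article does specify this model, listing its covariates, and it names group explicitly in the neighbouring model.

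Third, the size. At 0.40 SD on both changes the excess is within about one percentage point of nominal, and the larger figures need about 0.8 SD or more on both measures at once. This stands and limits the point.

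Fourth, a reader might take the phrase in "Association analysis between altered white matter microstructure imaging data and the assessments of cognitive function and depression" to mean that correlations are run only on tracts selected because they differed between arms. The sentence names no tracts and no selection rule, and it could equally refer to change over time. The documents do not support a selection charge.

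Finally, the analysis is exploratory in a pilot, and a group term would not establish mechanism: within-arm associations can still be confounded, and a single slope assumes that it is the same in both arms. That is correct. The term removes one known source of spurious association and no more.

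**Conclusion.** The change-on-change regression is specified without group and without saying which arms enter it, and the white-matter correlation names no group adjustment. That is a weakness in a stated model.

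Its consequence is conditional on two things: that the arms are pooled, and that the intervention shifts both the MRI measure and the outcome. Under those conditions the artefact is negligible at 0.40 SD on both, and becomes noticeable at about 0.8 SD on both. At still larger assumed differences it grows quickly. If only one measure shifts, it is absent.

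A reader should not conclude that any reported brain–behaviour association would be spurious; at the only effect size the article gives, the test behaves almost nominally. The point is a cheap improvement to a secondary, exploratory analysis, and it does not bear on the primary outcomes.

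**What to change.** - State for each change-on-change regression whether the arms are combined.
- Where they are combined, add group as a covariate alongside the three already named. Alternatively, report the within-arm slopes, accepting the few degrees of freedom that 12 per arm allow. If numbers permit, an interaction of group with MRI change would show whether a common slope is reasonable.
- For the white-matter association, replace the plain Spearman correlation with a partial Spearman correlation adjusted for group.

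The cost is a sentence or two of text and one residual degree of freedom per regression. No new data, scans or participants are needed.
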